### Hypothesis

Standard audiological care with one-on-one MI does not alter HA use compared to standard audiological care alone in new adult HA clients.

### Trial design {8}

This study will be a multi-center, prospective, randomized patient-blind controlled trial and employ a between-subject, pre- and post-tests design with a treatment and control group. It has been designed to be a superiority trial assessing motivational interviewing compared to standard audiological care. The SPIRIT (Standard Protocol Items: Recommendations for Interventional Trials) reporting guidelines were used to develop the methodology.

## Methods: participants, interventions, and outcomes

### Study setting {9}

Study participants will be recruited at audiology clinics located within the greater Vancouver region, British Columbia (BC), Canada. Audiology clinics will comply with WorkSafeBC and the Provincial Health Officer’s COVID-19 orders as related to safety plans. Audiologists will screen potential participants during the normal course of their work.

### Eligibility criteria {10}

Study eligibility criteria include new HA users who are **≥** 18 years old, with a Pure Tone Audiometric (PTA) hearing threshold above 25 dB in the worse ear at frequencies averaged across either 0.5, 1, 2, and 3 kHz or 4, 6, and 8 kHz (Table 1).

**Table 1 Tab1:** Inclusion and exclusion criteria

**Criteria**	**Description**
Inclusion	• 18 years and older • New hearing aid user • Unilateral or bilateral PTA hearing threshold above 25 dB in the worse ear across either 0.5, 1, 2, and 3 kHz, or 4, 6, and 8 kHz
Exclusion	• History of hearing aid use • Do not understand the English language • Unable to complete the online questionnaires in English language • Have inconsistent pure-tone audiometric readings • Have medical constraints that prohibit them from wearing hearing aids

Participants who have a history of HA use, do not understand English, do not respond reliably to audiometry, or have concurrent medical contradictions to HA use will be excluded.

Participants will be invited by the audiologists to undergo baseline assessment after screening.

### Who will take informed consent? {26a}

Written informed consent for study participation will be obtained by trained audiology clinic assistants. Completed consent forms will be forwarded to the study coordinator for secured documentation.

### Additional consent provisions for collection and use of participant data and biological specimens {26b}

No additional consent provisions for collection and use of participant data and biological specimens will be required.

### Interventions

#### Explanation for the choice of comparators {6b}

Participants in the control group will receive standard care as typically delivered by audiologists at in-person clinic visits with no additional treatment. Above comparator was selected to allow the effect of one-on-one MI on adherence to HA use to be compared with the current gold standard treatment of standard care. Audiologists will make treatment plans for new HA clients based on their personal experience, the evidence available from published studies, and expert opinion. There was no attempt to limit audiologists who deliver care in the comparator arm to ensure that the study outcomes can be generalized to the practice of non-study audiologists.

#### Intervention description {11a}

Patients allocated to the intervention group will attend a 30-min maximum one-on-one MI session hosted by a practicing MI therapist via Zoom at 1 month after the initial visit. Participants will also receive standard audiological care delivered at in-person clinic visits.

All control and intervention participants will be asked to attend 4 follow-up visits after the initial baseline assessment at 1, 3, 6, and 12 months. At follow-up visits, all participants will complete online International Outcome Inventory for Hearing Aids (IOI-HA) questionnaires and the study investigators will access each participant’s HA data-logging feature to determine the mean number of hours HAs were activated. Audiologist(s) will record the daily average hours of use based on the number of days since the last reading. All data will be entered using a secure online survey tool.

#### Criteria for discontinuing or modifying allocated interventions {11b}

The intervention and control groups are expected to have a low risk of adverse events. Interim visits not previously scheduled may be required for other reasons such as HA malfunctions. All events of accidental injury or participant withdrawal of consent during the trial will be recorded.

#### Strategies to improve adherence to interventions {11c}

At each study visit, adherence to the study intervention will be assessed in both the intervention and control groups. Strategies to improve adherence include:Individual assessment and instruction by study investigators and those involved.Participants will be contacted directly by telephone by study investigators if there are missed visits to encourage continued participation and to evaluate/assess barriers that prohibit participation.Telehealth follow-up visits with participating audiologists will be offered to those who may have limited access or who prefer telehealth.

#### Relevant concomitant care permitted or prohibited during the trial {11d}

There are no prohibitions on participants seeking or receiving unplanned care for HA malfunction or ear complaints during the course of the trial. All such visits and their purpose will be recorded.

#### Provisions for post-trial care {30}

There are no planned provisions for post-trial care other than standard care for HA clients which includes follow-up visits.

### Outcomes {12}

#### Primary outcomes

The primary outcome is the inter-group difference in average hours of HA use at 1, 3, 6, and 12 months post-intervention aimed at assessing the early and long-term effect of the intervention. This is a quantitative measure recorded by the HAs data-logging feature.

The secondary outcomes are differences in inter-group average participant-completed questionnaire (IOI-HA) [21] scores at 1, 3, 6, and 12 months post-intervention and reported complications. The IOI-HA is an established rigorous patient reported measure for HA effectiveness [22, 23].

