### Participant timeline {13}

Figure 1 demonstrates the participant timeline for this study. Participating audiologists will screen potential candidates in their normal day-to-day work. Signed consent and baseline assessment will be obtained from those who meet inclusion criteria and agree to participate in the study. All participants will have a 1-month follow-up after the initial assessment with an audiologist in-person or via telehealth where IOI-HA questionnaires will be administered, and HA data-logging will be accessed. Those in the intervention group will also undergo a 30-min one-on-one MI session after the 1-month follow-up visit and the details will be provided by the study coordinator. Subsequent follow-up visits will be conducted at 3, 6, and 12 months where participants will complete the IOI-HA questionnaire and their HA data-logging will be accessed.

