## Data collection and management

### Plans for assessment and collection of outcomes {18a}

Consented participants will be instructed about the study and its procedures. At the initial visit, data collection forms, including the email addresses of each participant, will be filled and collected by a trained audiology clinic assistant. This data will be securely stored on a password-protected device and transferred to the study coordinator and PI for long-term use and protection.

Outcome assessments of data-logged hearing hours and IOI-HA questionnaires will be performed at 1-, 3-, 6-, and 12-month time points after hearing aid fitting.

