#### Pre-intervention assessment at 1 month

Participants in both groups will continue to be contacted by their audiology clinics as required for standard care at the above-mentioned time point. Participants in the MI intervention group will attend a virtual one-on-one counseling session after their 1-month follow-up from hearing aid fitting. Teleconferencing software will be used to organize this meeting and instructions will be provided via email to each participant or a family member by study coordinator. The total time is anticipated to be approximately 30 min. This session will be hosted by a practicing MI therapist who will explore and elicit motivation in the participants to use their HAs for more hours.

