#### Post-intervention assessment at 3-, 6-, and 12-month follow-ups

Post interventions will be performed at 3-, 6-, and 12-month follow-ups from hearing aid fitting. During these follow-ups, in addition to standard care, participants will have the number of data-logged hearing hours per day extracted from their hearing device automatic data-logging feature and will be asked to complete the online IOI-HA questionnaires. The IOI-HA has been previously tested for its validity, reliability, and sensitivity [22, 23]. There have been suggestions that item 5 on the IOI-HA contributes inconsistently [22, 23]. However, the introspective subscale (items 1, 2, 4, and 7) of the IOI-HA was found to have a Cronbach’s alpha of 0.85 [23]. It has previously been used in other hearing aid outcome research [6].

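### The primary outcome treats the 1-month reading as post-intervention, although the protocol delivers motivational interviewing after that visit; the later time labels are also off by about a month

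*Protocol article*

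**What the plan says.** The section Primary outcomes defines the main endpoint thus: "The primary outcome is the inter-group difference in average hours of HA use at 1, 3, 6, and 12 months post-intervention". It says these time points serve to assess both the early and the long-term effect of MI. The secondary IOI-HA outcome is set at the same times: "scores at 1, 3, 6, and 12 months post-intervention and reported complications". Table 2 enters hours of use and IOI-HA at 1 month, in both arms, under its primary outcomes.

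Other sections of the protocol describe a different order of events:

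- Intervention description {11a} places MI "via Zoom at 1 month after the initial visit". It counts the four follow-up visits from the baseline assessment and has the audiologist average daily hours over the days since the previous reading.
- Participant timeline {13}: "Those in the intervention group will also undergo a 30-min one-on-one MI session after the 1-month follow-up visit". Hours and IOI-HA are collected at that visit.
- Plans for assessment and collection of outcomes {18a}: "Outcome assessments of data-logged hearing hours and IOI-HA questionnaires will be performed at 1-, 3-, 6-, and 12-month time points after hearing aid fitting".
- The next subsection is headed "Pre-intervention assessment at 1 month" and says MI participants "will attend a virtual one-on-one counseling session after their 1-month follow-up from hearing aid fitting".
- The subsection after that is headed "Post-intervention assessment at 3-, 6-, and 12-month follow-ups".

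**The concern.** The same 1-month reading is a post-intervention endpoint in one section and a pre-intervention assessment in another. Both cannot hold, and the conflict lies in the definition of the primary outcome.

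If the Primary outcomes section is followed as written, a comparison of the arms made before anyone has received MI would be reported as its early effect. A null result there could be taken as evidence that MI does not work early, and a positive one as evidence that it does. Neither conclusion would be warranted. The later results would carry follow-up times that the schedule does not deliver.

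**Working it through.** **Step 1. Background check on the plan's own figure.** Inputs from Sample size {14}: standardised difference 0.6, 5% significance, 80% power, 1:1 allocation. Sidedness is not stated; two-sided is assumed because it reproduces the result.

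- Normal approximation: n per arm = 2 × (1.960 + 0.842)² / 0.6² = 43.6, so 44.
- Exact noncentral t: power is 0.795 at 44 per arm and 0.804 at 45, so 45 per arm, as stated.
- Dropout of 50%: 45 / (1 − 0.5) = 90 per arm, 180 in total, as stated.

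The sample size stands and is not at issue here.

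**Step 2. Place the visits relative to MI.** Take MI at about month 1, just after that visit. Time since MI = visit month − 1.

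| Visit (months from the start of follow-up) | Label under Primary outcomes | Approximate time since MI | Label in the data collection section |
|---|---|---|---|
| 1 | 1 month post-intervention | 0, before MI | pre-intervention |
| 3 | 3 months post-intervention | 2 months | post-intervention |
| 6 | 6 months post-intervention | 5 months | post-intervention |
| 12 | 12 months post-intervention | 11 months | post-intervention |

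There are three post-MI readings, not four. Read literally, the Primary outcomes section would need visits at 1 + 1 = 2, 3 + 1 = 4, 6 + 1 = 7 and 12 + 1 = 13 months. No schedule in the protocol has these.

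**Step 3. What the 1-month reading contains.** Each reading averages hours since the last one. The first therefore covers the time up to the 1-month visit, all of it before MI in both arms. The 1-month IOI-HA is also completed at that visit. The 3-month reading, covering about months 1 to 3, is the first that can show an effect of the session.

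**Step 4. Consequence for a test.** Statistical methods {20a} names an independent-samples t-test for hours. With 45 per arm:

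- Post-MI visit with a true standardised difference of 0.6: noncentrality 0.6 × √(45/2) = 2.85, power 0.804.
- 1-month visit with a difference of 0 due to the session: rejection probability 0.05, whatever MI does later.

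**Step 5. Time origins.** Three are in use: the initial or baseline assessment (Intervention description, Participant timeline), hearing aid fitting (the data collection section) and the intervention (Primary outcomes). Table 2 does not settle the order, because MI and the 1-month outcomes share one column.

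**The case against.** **Could intervention mean the fitting?** On that reading the Primary outcomes labels would agree with {18a}. But the protocol uses the word for MI, and the two data collection headings set pre- and post-intervention relative to MI. The reading does not hold.

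**Is it only a drafting slip?** Quite possibly. The data collection section already has the right split, which points to loose wording in the endpoint definition rather than a flawed design. The wording still sits in the primary outcome and is repeated by Table 2's classification, and nothing elsewhere corrects it.

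**Is a one-month error trivial?** For the later visits, largely yes: 11 against 12 months hardly changes a long-term conclusion. A reader might infer that the long-term aim cannot be met, but the documents do not support that. The 1-month reading is the substantive defect.

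**Does the 1-month reading dilute the result?** A reader might infer that averaging it with later visits would cost power. The protocol plans no such pooling. If the visits are tested separately, the 1-month test takes nothing from the others.

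**Is a 1-month difference necessarily chance or imbalance?** That would go too far. Allocation is at day 0. The Discussion says masking lasts until participants learn of their MI appointment, and no section says this comes after the 1-month reading. The blinding section says audiologists and investigators are not blinded at outcome collection. Anticipation or differing care could produce a difference. What stands is narrower: the reading cannot reflect the session itself.

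**Conclusion.** The protocol contradicts itself on the time points of its primary and secondary outcomes. One of the four, the 1-month reading, precedes MI and cannot measure its effect. A test there has about a 5% chance of rejecting, against about 80% at a post-MI visit under the planned effect. The other three labels overstate time since MI by about one month.

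The conclusion rests on MI following the 1-month visit, as two sections say. The 5% also assumes no anticipation or difference in care before the session. The one-month shift is approximate, because the gap between visit and session is not given. The contradiction itself depends on none of these numbers, nor on the figure not shown or a separate analysis plan. It should be corrected before the outcomes are analysed.

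**What to change.** In the Primary outcomes section and Table 2:

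1. State one time origin and use it for every visit.
2. Define the between-arm comparisons of hours and IOI-HA at 3, 6 and 12 months from that origin.
3. Class the 1-month hours and IOI-HA as the pre-intervention measurement and take them out of the outcome comparisons.

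Reconcile Intervention description {11a}, Participant timeline {13}, the data collection section {18a} with its two subsections, and Table 2 with that definition, including the order of the 1-month visit and MI. The abstract gives only follow-up times without the post-intervention label, so it needs no change on this point.

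Reclassifying also supplies a measure of hours before MI. The trial's pre/post design calls for one, and Table 2's baseline rows, which hold only audiometry and word recognition, do not provide it.

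The cost is a formal amendment approved by the review board, which the protocol requires for changes of this kind; recruitment began in March 2021. Visits, data collected and sample size stay as they are.

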#### Hearing aids

Many studies demonstrate that hearing aid (HA) use increases the user’s ability to detect, differentiate, and locate sound and improve speech recognition and health-related quality of life (HRQoL). A review by Chisolm et al. [3] assessed the effect of amplification on HRQoL and concluded that HAs had a medium-to-large effect. Other reviews on the effects of HAs on quality of life have reached similar conclusions [4, 5].

Despite these findings, HA uptake and use are generally poor. A UK National Health Service survey indicated that approximately 40% of new patients use their HAs for less than 4 h a day [6]. Similar conclusions have been reported in other comparable countries [7, 8]. Reasons for this lack of use include disappointment with HA effectiveness, perceived lack of need for a HA, affordability or cost concerns, and the social stigma [9–11].

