### Objectives {7}

The primary objective is to determine the efficacy of one-on-one MI in increasing adherence to HA use in new adult clients in the short and long terms. The secondary objective is to determine if there are adverse effects associated with one-on-one MI.

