### Methods in analysis to handle protocol non-adherence and any statistical methods to handle missing data {20c}

Sample population to be analyzed will be based on randomization. Any participant’s missing age data will be imputed with the mean of age of their allocation group. Missing sex data will not be analyzed. Participants without or with incomplete main outcome data including data-logged HA use hours and IOI-HA scores will be excluded from analysis.

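### Participants who return the hearing aid, or stop for good and have no readable log, are excluded although their use is known to be 0 h/day

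*Protocol article*

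**What the plan says.** All references are to the protocol article.

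- Objectives {7}: the aim is to "determine the efficacy of one-on-one MI in increasing adherence to HA use in new adult clients in the short and long terms".
- Outcomes {12}: "The primary outcome is the inter-group difference in average hours of HA use at 1, 3, 6, and 12 months post-intervention". The next statement on measurement is "This is a quantitative measure recorded by the HAs data-logging feature", and no other source for hours is named.
- Intervention description {11a}: "Audiologist(s) will record the daily average hours of use based on the number of days since the last reading".
- Missing data {20c}: the section opens with "Sample population to be analyzed will be based on randomization" and ends with "Participants without or with incomplete main outcome data including data-logged HA use hours and IOI-HA scores will be excluded from analysis".
- Retention {18b}: data gathered before a withdrawal are kept and analysed. Nothing is assigned for the time after it.

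No section gives a value to a participant who no longer has a device to read. Return of the aid is not mentioned.

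**The concern.** The trial is about adherence, and giving the aid up is the most complete form of non-adherence. Once an aid has gone back there is no log, but use of it is not unknown: it is zero from that date. The exclusion rule in {20c} treats this known zero like an unknown value and removes the participant.

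The MI session takes place after the 1-month visit, so later abandonment follows both randomisation and the intervention. The background section gives disappointment, no felt need, cost and stigma as reasons for low use, and MI is meant to work on ambivalence of that kind. A comparison limited to people with a log therefore conditions on something the intervention may change. If MI works partly by keeping people from giving up, that part of its effect cannot appear in the primary analysis. If more people give up in the MI arm, the logged hours will flatter MI.

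**Working it through.** **1. The plan's own figure.** Sample size {14} uses a standardised difference of 0.6, 5% significance and 80% power. By the normal approximation, n = 2 × (1.96 + 0.84)² / 0.6² = 43.6, so 44 per arm. The exact t-test gives 44.6, so 45. With the 50% dropout allowance, 45 / (1 − 0.5) = 90 per arm, 180 in total. The figure reproduces and is not in dispute. It shows that the design tolerates up to 45 of 90 participants per arm without an outcome, all of whom {20c} would remove.

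**2. Who is affected.** Set {11a}, {12} and {20c} side by side:

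| Situation at the visit | Log | Under {20c} |
|---|---|---|
| Aid kept, little worn or unworn, attends | low or zero daily average | stays in, if the IOI-HA is complete |
| Aid returned | none | excluded, use known to be 0 |
| Permanently stopped, no readable log | none | excluded, use 0 if documented |
| Malfunction or lost contact | none | excluded, use unknown |

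The point concerns the second and third rows only.

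**3. Possible size.** The documents give no return rate, mean or SD, so these are assumptions: users' mean m = 6 or 8 h/day and SD s = 4 h. Let p be the share in an arm with known zero use and no log. With zeros counted, the arm mean is (1 − p)m and the variance is (1 − p)(s² + m²) − [(1 − p)m]². The standardised difference divides by the root of the average of the two variances.

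*(a) MI halves stopping and users' hours do not change.* The log-only difference is 0 h. With zeros counted it is (p_control − p_MI) × m:

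| Stopping, control vs MI | m = 6 | m = 8 |
|---|---|---|
| 10% vs 5% | +0.3 h | +0.4 h |
| 20% vs 10% | +0.6 h | +0.8 h |
| 30% vs 15% | +0.9 h | +1.2 h |

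The standardised values run from 0.07 to 0.25.

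*(b) Users differ by 0.6 SD (2.4 h) and stopping is 20% in both arms.* Log-only: 2.4 h, 0.60 SD. With zeros and m = 8: 0.8 × 10.4 − 0.8 × 8 = 1.92 h. The variances are 30.1 and 23.0, the SD is 5.15, and 1.92 / 5.15 = 0.37. With m = 6 the difference is again 1.92 h and the SD 4.62, giving 0.42.

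*(c) Users differ by 2.4 h and stopping is 10% in control, 20% with MI.* Log-only: 0.60 SD. With zeros: 0.8 × 10.4 − 0.9 × 8 = 1.12 h (m = 8, 0.22 SD) or 0.8 × 8.4 − 0.9 × 6 = 1.32 h (m = 6, 0.29 SD).

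The log-only result hides an effect in (a) and overstates it in (b) and (c).

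**The case against.** **Most stopping is captured.** A reader might infer that everyone who stops wearing the aid leaves the comparison. The documents do not support that. Hours are averaged over the days since the last reading, so an unworn aid brought to the visit gives a low or zero value. This objection stands and limits the point to returned aids and permanent stops with no readable log.

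**The outcome sentence excludes nobody.** It names a measuring instrument, and an objective log is a reasonable choice. That is right: the exclusion comes from {20c}, and the outcome definition matters only because it offers no other way to record zero use.

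**The loss figures are not return figures.** A reader might take the 50% allowance, or the 39.1% unavailable in an earlier local trial, as a measure of abandonment. Sample size {14} attributes the first to pandemic uncertainty and the second to missed follow-up or incomplete questionnaires. The number of known zeros is undocumented.

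**Sign reversal.** A reader might conclude that a helpful intervention would look harmful. One can construct this. Of 100 controls, 25 return the aid and 75 wear it 8 h; MI persuades 10 of the 25 to keep it at 3 h. Logged users then show 8.0 h against 630/85 = 7.41 h, while with zeros counted it is 6.0 h against 6.3 h. The arithmetic is right, but every input is invented, and the scenarios worked above give no reversal. It is possible, not shown to be likely.

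**Timing and estimand.** Returns before the MI session cannot be prevented by it, so zeros from that period add noise. Scoring a stop as zero is also one estimand choice among several, of a kind often left to an analysis plan. Both are fair, but the protocol does not leave the matter open: it prescribes exclusion.

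**Conclusion.** The point holds in this limited form. Taken together, {12} and {20c} remove participants whose outcome is known, on the basis of a post-randomisation event tied to the objective. That conflicts with the as-randomised population in the same section and sits badly with {18b}. Neither the size nor the direction of the bias can be computed from the documents. Under the assumed 6 to 8 h/day and SD of 4 h, the log-only comparison may show nothing where the difference among all randomised is +0.3 to +1.2 h, or 0.60 SD where it is 0.22 to 0.42 SD. These ranges show that the rule can matter; they do not predict what this trial will see.

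**What to change.** Amend {20c} and the outcome definition in {12} so that a participant with documented return or permanent non-use of the aid and no readable log is analysed as randomised and scored 0 h/day from the documented date. Exchange for another device is not a stop. Reserve missing status for use that is truly unknown, such as malfunction or lost contact. Say also that the hours comparison does not require a complete IOI-HA; otherwise the joint condition in {20c} would still remove these participants.

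Record the date and reason at the visit, or in the telephone call after a missed visit that {11c} already plans. That is one field and a few words of protocol text.

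There are two costs. Hours will cluster at zero, so the analysis must tolerate skew. The standardised difference may also fall below the planned 0.6: it is about 0.4 in scenario (b), which needs 2 × (1.96 + 0.84)² / 0.4² = 98 per arm. The known zeros add some analysable participants (if 45 per arm have a log and zeros are 20% of those analysed, 45 / 0.8 = 56), but not enough to close that gap. The sample-size basis should be looked at again with the change.
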